#### Secondary hypotheses

2.2.2

Compared to those allocated to the usual care group, 1) carers in the intervention group will report (a) an improved mean score on the Caregiving Self-Efficacy Scale and (b) an improved mean score on the Quality of Social Support Scale; 2) their care recipients will report (via proxy ratings) (a) a reduced mean score on the Revised Memory and Behaviour Problem Checklist and (b) fewer unplanned hospital admissions, less emergency department uses and less use of permanent residential aged care at 12 months; and, (c) better quality care experiences via proxy ratings; and 3) provision of the culturally tailored iSupport model will be cost-effective compared to usual care.

### Research questions for the process evaluation

2.3

We will explore the two research questions in the process evaluation: 1) what are the strategies that enable aged care organisations, staff and carers of people with dementia to embed the iSupport model in real care settings; and 2) what are the barriers that impede stakeholders from embedding the iSupport model in real care settings?

### Methods

2.4

#### Design

2.4.1

A pragmatic, multicentre hybrid type I effectiveness–implementation randomised controlled trial will be conducted. This design enables the concurrent evaluation of the effectiveness of the culturally tailored iSupport model and the implementation strategies under real‑world conditions. A hybrid type I design was selected in preference to other hybrid designs because there is currently limited evidence to guide the implementation of the culturally tailored iSupport model within aged care organisations. The intervention will be delivered over a 12‑month period. Fig. 2 present the CONSORT flow chart.

**Fig. 2 fig0002:**
[figure not shown]
CONSORT flow chart.

A process evaluation will examine contextual factors influencing implementation, implementation fidelity, and the mechanisms through which the intervention produces change (Moore et al., 2015). The trial was registered with the Australian New Zealand Clinical Trials Registry on 5 June 2025 (ACTRN12625000587404). Further information is available in the enclosed “Information about trial registration data”.

#### Study setting, participants and sample size

2.4.2

This study will be undertaken in community aged care settings managed by seven ethno‑specific aged care organisations located in three states in Australia. The estimated minimal sample size for carers in the study is 100 with 50 carers in the intervention group and 50 in the usual care group. This sample size is based on a primary outcome of the mental component of the 12-Item Short-Form Health Survey and an assumption of a 0.57 effect size reported in a previous trial using a multicomponent intervention for carers of people with dementia (Berwig et al., 2017), with an 80% power to detect a difference between means of 4.93 with a pooled standard deviation of 8.63 in the study. However, considering a 50% attrition rate in a 12-month trial in our previous project, we will need to recruit 150 carers to the trial or 75 carers in the tailored iSupport group and the usual iSupport group respectively.

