##### Intervention effectiveness

2.4.7.1

Data analysis will be led by a statistician who will be blinded to group allocation. All analyses will be conducted according to the intention‑to‑treat principle, with participants analysed in their assigned groups. Multivariable linear mixed‑effects models will be used to examine differences in primary and secondary outcomes between groups over time. Given the repeated measurements for each participant, mixed‑effects models will account for both fixed and random effects within the hierarchical data structure. Fixed effects will include group, time, and group‑by‑time interaction terms, while random effects will model individual‑level variability in intercepts to account for within‑participant correlation. Models will be adjusted for baseline values of the outcome variables. Maximum likelihood estimation will be used to assess between‑group differences and changes over time.

Univariate mixed‑effects models will be fitted initially, followed by multivariate models incorporating variables identified as clinically relevant or statistically significant in univariate analyses to control for potential confounding. Model building will involve sequential addition and removal of covariates, with changes in model fit evaluated using log‑likelihood statistics to determine the final multivariate model. All statistical tests will be two‑sided, with statistical significance set at p < 0.05. Analyses will be performed using Stata version 16.1 and R version 4.2.2.

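### The recruitment target of 150 covers 33% attrition, not the 50% the plan assumes; at 50% loss, unadjusted power is about 68%, not 80%

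*Protocol article*

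**What the plan says.** Section 2.4.2 (Study setting, participants and sample size) sizes the trial on the mental component of the SF-12. It takes "an assumption of a 0.57 effect size reported in a previous trial" and gives "80% power to detect a difference between means of 4.93 with a pooled standard deviation of 8.63". The resulting requirement is: "The estimated minimal sample size for carers in the study is 100 with 50 carers in the intervention group and 50 in the usual care" arm.

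The attrition step follows directly: "considering a 50% attrition rate in a 12-month trial in our previous project, we will need to recruit 150 carers to the trial", that is, 75 per group. The Abstract repeats 150 in total and 75 per group.

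The significance level is set in section 2.4.7.1 (Intervention effectiveness): "All statistical tests will be two‑sided, with statistical significance set at p < 0.05". The primary hypotheses (2.2.1) are set at 12 months.

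**The concern.** The two steps of the paragraph do not fit together. The first says that 100 carers are the minimum for 80% power. The second presents 150 recruits as the allowance for losing half of them, but half of 150 is 75.

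The figure of 150 is what results from adding the attrition percentage to the requirement, when the requirement should be divided by the proportion retained. The slip is minor at low attrition and large at 50%.

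At stake is the power claim for the outcome that sizes the trial. If the plan's attrition assumption comes true, the trial ends with a quarter fewer carers than its own stated minimum. A null result would then be read as coming from a trial with 80% power when its own assumptions give less.

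**Working it through.** **Inputs**
- Difference 4.93, SD 8.63, power 80%, minimum 50 per group, attrition 50%, target 150: section 2.4.2.
- Two-sided 0.05: section 2.4.7.1.
- Standardised effect: 4.93 / 8.63 = 0.571, which agrees with the stated 0.57.

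**Step 1: reproduce the requirement of 50 per group.**
- Normal approximation: n = 2(1.960 + 0.842)² / 0.571² = 48.1, so 49 per group.
- Two-sample t-test: 49.1, so 50 per group. Power at 50 per group is 80.7%.
- A one-sided 0.05 test would need only about 39 per group, so it is not the basis of the stated figure.

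The requirement of 100 completers is sound and comes from an unadjusted two-sided comparison of two means.

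**Step 2: the attrition allowance.**
- Correct formula: N recruited = N needed / (1 − attrition) = 100 / 0.50 = 200.
- Formula that gives the stated target: 100 × (1 + 0.50) = 150.
- Completers from 150 at 50% attrition: 150 × 0.50 = 75.
- Attrition at which 150 still leaves 100 completers: 1 − 100/150 = 33.3%.

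**Step 3: power at 75 completers (37 and 38 per group; t-test, two-sided 0.05).**

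| Quantity | 50 per group | 37/38 per group |
|---|---|---|
| Power for 4.93 points | 80.7% | 68.5% |
| Chance of missing a true 4.93-point difference | 19.3% | 31.5% |

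The standardised difference detectable with 80% power at 37/38 is 0.6557, or 0.6557 × 8.63 = 5.66 points. That is above the 4.93 used for design and above the 5-point difference in primary hypothesis 1(a). Power for exactly 5 points is 69.7%.

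**Step 4: effect of baseline adjustment.** Section 2.4.7.1 plans models adjusted for the baseline value. With a baseline-to-12-month correlation r, the effective standardised difference is 0.571 / √(1 − r²). The article does not give r, so the values below are assumptions.

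| r (assumed) | Effective standardised difference | Power at 37/38 |
|---|---|---|
| 0.3 | 0.599 | 72.5% |
| 0.4 | 0.623 | 75.9% |
| 0.5 | 0.660 | 80.5% |
| 0.6 | 0.714 | 86.2% |

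Power reaches 80% at r of about 0.49.

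**The case against.** The strongest reply is that 68% describes an unadjusted comparison of completers, which is not the planned analysis. The plan is a baseline-adjusted mixed model fitted by maximum likelihood under intention to treat. With a correlation of about 0.5 or more, 75 completers would give 80% power after all, and carers lost between 6 and 12 months would still contribute their 6-month data. This stands as a qualification of the consequence: the power actually achieved could be above 68%, by an amount the document does not let us fix. It does not rescue the target. The sample-size paragraph uses no correlation, its 50 per group is reproduced without one, and 150 does not follow from an adjusted calculation.

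A second reply is that 50% may be pessimistic. It comes from an earlier project, and section 3.1 reports strong retention in the feasibility study of this model. At attrition of 33% or less, 150 is enough. But section 3.1 gives no retention figure, it also reports high attrition in iSupport trials in other countries, and section 2.4.2 offers no planning rate other than 50%.

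A third reply is that the 80% is attached to the minimum of 100 carers and is correct for that number. That is true: the error lies only in the step from 100 to 150. But the step is presented as securing those 100 carers under 50% attrition, and it does not.

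This is not a matter of detail left to a fuller document. The article states every input and draws a wrong result from them.

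**Conclusion.** The concern holds. The base calculation is right and the attrition step is wrong. A target of 150 protects the stated minimum of 100 completers only up to 33.3% attrition; at the plan's 50% it leaves 75.

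Power for the design difference is then 68.5% (t-test; a normal approximation gives about 70%), against 80.7% at 50 per group. This rests on the plan's own difference, SD, two-sided 0.05 level and attrition rate, with losses spread evenly over the groups and no baseline adjustment, as in the plan's own calculation. Under the planned adjusted model the figure would be higher, 72.5% to 86.2% for assumed correlations of 0.3 to 0.6, but nothing in the document shows which value applies.

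The statement is wrong as written and should be corrected. The article describes the trial as not yet recruiting, so on that status the correction can be made before any data accrue.

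**What to change.** Correct section 2.4.2 so that the target, the attrition rate and the power agree. The target can stay at 150 under either of the first two options.

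- **(a) Restate what 150 delivers.** Say that 150 recruits retain 100 completers if attrition is no more than 33%, and that at 50% attrition 75 completers give about 68% unadjusted power, with 5.7 points detectable at 80% power. If about 33% is now the expected rate, give the grounds for it.
- **(b) Base the power on the planned analysis.** State the power at 75 completers for the baseline-adjusted model, with the assumed correlation, its source and a range. About 0.5 is needed for 80%, so the value should come from data and not be chosen because it restores the claim.
- **(c) Raise the target.** If 80% unadjusted power at 50% attrition is to stand, the target is 200 (100 per group).

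Whichever is chosen, the text should no longer say or imply that 150 covers 50% attrition.

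Options (a) and (b) cost a rewritten paragraph. Under (a) the stated power becomes less favourable; neither needs extra carers, and conduct, endpoints and analysis are unchanged. Option (c) costs 50 more recruits and a matching change in the Abstract.

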##### Inclusion and exclusion criteria for carers

2.4.2.1

Inclusion criteria for carers: 1) Carers speak one of these languages at home: Italian, Greek, Mandarin, Cantonese, Vietnamese, Bahasa or Spanish; 2) Carers are aged 18 years or over; 3) Carers provide care for older people (aged greater than or equal to 65) living with dementia from a culturally and linguistically diverse background at least twice a week. If the care recipients have not been formally diagnosed with dementia but meet cognitive impairment using the ‘AD8 Dementia Screening Interview’ with score equal or greater than 2 (Galvin et al., 2005). Exclusion criteria: 1) Carers have self-reported terminal health conditions that may significantly affect their ability to participate in the study; and 2) Carers are involved in other studies.

##### Inclusion and exclusion criteria for staff

2.4.2.2

Staff will be invited to participate in the process evaluation if they meet these criteria: 1) providing direct care services to people with dementia from one of the seven language groups; 2) having dementia care experience for at least 3 years. Staff will be excluded from the study if they are agency staff.

#### Randomisation

2.4.3

Following completion of baseline data collection, carers will be randomly allocated to either the intervention group or the usual care group. Block randomisation will be used to ensure balanced allocation to each treatment group within each recruitment site. Stratification will be incorporated into the block randomisation to ensure comparable distribution of spouse versus non‑spouse carers and similar stages of dementia among care recipients across the two groups. Randomisation will be conducted using R software version 4.3.2 by a statistician on the research team who will be blinded to participant identities and will not be involved in outcome assessment or data analysis. Group assignments will be put in sequentially numbered, opaque and sealed envelopes and opened only after each participant has completed baseline data collection.

#### Interventions

2.4.4

##### The intervention group

2.4.4.1

Participants in this group will receive the culturally tailored iSupport model, comprising facilitator-enabled four intervention components over a 12‑month period.

###### Component 1: A psychoeducation program

2.4.4.1.1

First, trained facilitators will engage carers in a learning needs assessment using an adapted version of the Risk Appraisal Measure (Czaja et al., 2009). This assessment incorporates recommendations for relevant learning units from the iSupport program and unfolding case studies drawn from the “Culturally tailored case studies for dementia carers”. Based on the assessment, carers will select the recommended learning units and case studies to develop an individualised study plan and complete these at their own pace. Carers will be encouraged to reassess their learning needs and modify their study plans throughout the 12‑month intervention period in response to changes in their care recipients’ circumstances. The expected time commitment for the psychoeducation program is approximately 10–20 min per week. Engagement with the educational content and completion of study plans will be monitored through an intervention audit. All psychoeducation resources will be made available in carers’ preferred language and delivery format, including web‑based learning, e‑books, or printed hard‑copy materials.

###### Component 2: Facilitator‑enabled carer peer support

2.4.4.1.2

The facilitator will assign carers to peer support groups of 5–10 participants and will facilitate monthly online meetings via platforms such as WhatsApp, WeChat, or Microsoft Teams. Each meeting will last approximately 45–60 min. A standardised meeting agenda will be used to guide discussions, with a focus on carers’ experiences of the psychoeducation component, including learning processes, challenges, and outcomes. Meetings will be recorded and made available to carers within the same group for later review, as needed. Between meetings, facilitators will encourage carers to engage in weekly group interactions through text messaging, sharing resources, or informal discussion via WhatsApp, WeChat, or other agreed social platforms to strengthen social connectedness and peer support.

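### Intervention carers are treated in peer groups and controls are not, but the stated model has only a carer-level random intercept, so the standard error of the arm difference is too small if outcomes correlate within groups

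*Protocol article*

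**What the plan says.** Carers are randomised one by one, in blocks within recruitment site (section 2.4.3). Three parts of the protocol article then matter.

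- **Delivery.** In the intervention arm, "The facilitator will assign carers to peer support groups of" 5–10 (section 2.4.4.1.2). Each group has monthly facilitated meetings, recordings shared within the group and weekly messaging. The facilitator also supports service navigation and coaching (section 2.4.4.1.3). Controls are pointed to websites with a flyer (section 2.4.4.2), so their treatment creates no groups.
- **Model.** Section 2.4.7.1 lists group, time and their interaction as fixed effects, with adjustment for the baseline outcome. The random effects are for individual-level "variability in intercepts to account for" correlation within a participant. The text mentions a hierarchy in the data, but introduces it with the repeated measurements on each participant. No peer-group or facilitator term is named. "All statistical tests will be two‑sided", "with statistical significance set at p < 0.05".
- **Sample size.** "The estimated minimal sample size for carers in the study is 100", that is, "50 carers in the intervention group and 50 in the usual care group", on "an assumption of a 0.57 effect size" and "80% power to detect a difference between means of 4.93 with a pooled standard deviation of 8.63" (section 2.4.2). Recruitment is set at 75 per arm. No design effect appears.

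**The concern.** A carer-level intercept deals with several measurements on one carer. It still treats two carers in the same peer group as independent. Carers who meet monthly for a year under one facilitator may come to resemble each other on the outcomes. The article itself gives grounds to expect this. Section 1.1.2 credits peer support with role modelling, greater self-efficacy and less stress, and section 3.2 notes that facilitators differ in experience and competence.

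Positive correlation of this kind makes the variance of the intervention-arm mean larger than the model assumes, and nothing offsets it in the control arm. Confidence intervals for the arm difference would then be too narrow on the primary and secondary outcomes, and the planned number would buy less power than stated.

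**Working it through.** **Inputs from the article.** Difference 4.93, SD 8.63, two-sided alpha 0.05, power 80%, 50 analysed per arm from 75 recruited, peer groups of 5–10.

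**Assumptions.** The ICC (ρ) is not in the document; 0.02 to 0.10 is used. It means the correlation due to peer group or facilitator beyond site. Losses are spread evenly over groups, and total variance is equal in the two arms.

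**Step 1: the plan's own figure.** n per arm = 2 × [8.63 × (1.960 + 0.842) / 4.93]² = 48.1, so 49 by the normal approximation; the noncentral t gives 50 (power 80.7%). The stated 50 per arm is therefore a plain two-sample calculation with independent carers. At 50 per arm the unclustered standard error is 8.63 × √(2/50) = 1.726, and normal-approximation power is 81.5%.

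**Step 2: groups.** 75/10 = 7.5 and 75/5 = 15, so about 8 to 15 groups. If 50 of 75 are analysed, groups of 5 and 10 average 5 × 50/75 = 3.3 and 10 × 50/75 = 6.7 analysed carers (m).

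**Step 3: formulas.** Clustering inflates the variance in one arm by 1 + (m − 1)ρ, so the variance of the arm difference is inflated by

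V = 1 + (m − 1)ρ/2.

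- True standard error = 1.726 × √V
- Actual type I error of the unadjusted test = 2 × [1 − Φ(1.96/√V)]
- Power of a test using the correct standard error = Φ(4.93/(1.726√V) − 1.96)
- Analysed number needed per arm = 48.1 × V

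**Step 4: results at 50 analysed per arm.** Example, m = 6.67 and ρ = 0.05: V = 1 + 5.67 × 0.05/2 = 1.142; √V = 1.068; standard error 1.844; 1.96/1.068 = 1.83, giving 6.7%; power Φ(2.67 − 1.96) = 76%.

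| ICC (assumed) | SE too small by a factor of | Type I error | Power | Needed per arm |
|---|---|---|---|---|
| 0 | 1.000 | 5.0% | 81.5% | 49 |
| 0.02 | 1.012–1.028 | 5.3–5.7% | 81–79% | 50–51 |
| 0.05 | 1.029–1.068 | 5.7–6.7% | 79–76% | 51–55 |
| 0.10 | 1.057–1.133 | 6.4–8.4% | 77–71% | 54–62 |

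In each range the first value is for m = 3.3 and the second for m = 6.7.

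**Step 5: check by simulation.** With full groups of 5 and 10 and an unadjusted t-test (8,000 runs per setting), rejection under no effect was 5.6% and 6.0% at ICC 0.02, 6.4% and 7.8% at 0.05, and 7.3% and 9.8% at 0.10. The formulas for the same full groups give 5.5% and 6.0%, 6.2% and 7.7%, and 7.4% and 10.4%. The direction and scale agree.

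**The case against.** The best case for the plan has four parts.

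- **The ICC is unknown and may be small.** Study plans are self-paced, and navigation and coaching are one-to-one. Randomisation is blocked within site, so correlation from site or language common to both arms does not make the standard error too small. Only the part due to peer group or facilitator counts. This stands, and it limits the size of the point. It does not remove the structure, because the facilitator is shared and the peer component is a group treatment.
- **Attrition shrinks the groups.** This stands and is built into the table.
- **Covariate selection might bring in site, or an analysis plan might add a term.** A site covariate would not represent peer groups. The random effects are written out in the article, so a group term would change the stated model; it would not fill in a detail left open.
- **Maximum likelihood is adequate for the planned model.** This stands. The planned intercept is per carer, with up to 150 carers. The tendency of maximum likelihood to understate a variance from about 8–15 groups matters only once a group term is added.

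A reader might also infer three stronger things that the documents do not support. First, that the error favours the intervention: the tests are two-sided and the estimate is not biased, so false positives rise in both directions. Second, that type I error reaches about 9–10%: that needs full retention and an assumed ICC of 0.10. Third, that power at 50 per arm falls to 73–76% at ICC 0.05: that pairs the number left after losses with groups that have lost nobody. A calculation with one facilitator per site would likewise be conjecture, since the number of facilitators is not given.

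**Conclusion.** The point holds in a limited form. The design is individually randomised with clustering by treatment in one arm, the stated model ignores that clustering, and so does the sample size. The structural finding rests on the text alone.

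The size does not. At the plan's 50 analysed per arm and an assumed ICC of 0.05, type I error is about 0.7 to 1.7 percentage points above nominal and power is about 2 to 5 points below 81.5%. The effect is small at ICC 0.02 and zero at ICC 0. The formulas describe a single-time-point comparison; for the baseline-adjusted repeated-measures model, the relevant ICC is that of the outcome after adjustment. This is a specification to correct before the analysis. It does not undermine the design.

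**What to change.** **Section 2.4.7.1**

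- Record peer-group and facilitator ID for every intervention carer in the trial dataset. Facilitators make the assignments, so the information exists. The registration entry says the trial is not yet recruiting, so it can be captured prospectively.
- Add a random effect for peer group that applies in the intervention arm only, with each control as a singleton, and keep the carer-level intercept for the repeated measures.
- Report the final model by REML with Satterthwaite or Kenward-Roger degrees of freedom. Keep maximum likelihood for any log-likelihood comparison of fixed effects, because REML likelihoods are not comparable across models with different fixed effects.

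**Section 2.4.2**

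- Restate power over a stated range of ICCs and analysed group sizes, as in the table.

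**Cost.** Two ID fields and one model term. Intervals will be slightly wider and the stated power lower. The group variance will be imprecise with about 8–15 groups and may be estimated as zero, so the plan should say what is reported in that case. The cluster structure could reveal the arms to the blinded statistician; fixing the analysis code on a dummy allocation first deals with this.
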